#### Plans to promote participant retention and complete follow-up

This clinical trial will provide no incentives to increase participant retention. To reduce the burden on participants, they will be given the choice to attend in-person evaluations (at home or in a health care center) and/or receive telephone calls. The technical staff in charge of the evaluation and the data collection, along with the clinicians that deliver the interventions, will be reminded to keep an up-to-date record of the participants’ contact information in order to prevent data loss during the follow-up stage. Participants who decide to withdraw from the study will no longer complete follow-up evaluations. An informed consent revocation form will be provided for these cases.

#### Data management

The data collected from each participant will be directly stored in electronic forms by the recruiters or the outcome evaluators during the trial. After completion, these electronic forms will be submitted online, through a secure platform, to be automatically downloaded to a unique and encrypted database. No copies of the data will be kept on the electronic devices used in the study (e.g. smartphones, tablets, personal computers). Data will be stored in a centralized database by the researchers in charge of administering trial data. Data verification procedures will be conducted weekly to identify missing or mistaken values.

#### Confidentiality

Participant’s sensitive data and identification will be replaced with a set of unrelated characters (ID code). This will make it possible to work with coded and anonymized data, thus safeguarding the participants’ confidentiality. As detailed in the “Data management” section, data will be encrypted and securely kept, with access being supervised and centralized by the researchers in charge of administering trial data, who will access them using passwords.

#### Plans for collection, laboratory evaluation and storage of biological specimens for genetic or molecular analysis in this trial/future use

Not applicable.

### Statistical methods

#### Statistical methods for primary and secondary outcomes

Results will be reported according to the Consolidated Standards for Reporting Trials (CONSORT), specifically its extensions for cluster randomized clinical trials and clinical trials of non-pharmacological interventions [47, 48]. We will check the balance between the baseline characteristics of the intervention groups. As a general rule, for dichotomous or categorical variables, we will present the percentage and frequency of each category of interest (e.g. response vs. no response to treatment) for each intervention group, along with the odds ratio (OR) as a measure of the effect, a 95% confidence interval (95% CI), and *p* value. For continuous variables, we will present the means and standard deviations for each intervention group, along with the mean difference between the groups, 95% CI, and *p* value. For the analysis of dichotomous outcomes (including the main outcome), we will fit logistic random effects regression models to reflect the grouped nature of the data and will report OR, with their respective 95% CI, as effect size measures. The same strategy will be used for continuous outcomes (i.e. difference in means between the groups) with linear random effects regression models and Cohen’s *d* (i.e. standardized mean difference), with their respective 95% CI, as effect size measure. These analyses will be assisted using Stata 14.0 [49].

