### Hypotheses

The proportion of patients with improvement in depressive symptoms will be 23% higher in the “Me cuido y me siento mejor” primary care clinics compared to the enhanced usual care primary care clinics, at 6-month follow-up.The proportion of patients recovered from depression would be higher in the “Me cuido y me siento mejor” compared to the enhanced usual care primary care clinics, at 6-month follow-up.Patients in the “Me cuido y me siento mejor” primary care clinics would have better social problem-solving skills and health-related quality of life than patients in the enhanced usual care primary care clinics, at 6-month follow-up.Patients in the “Me cuido y me siento mejor” primary care clinics would have lower blood pressure and improved glucose regulation than patients in the enhanced usual care primary care clinics, at 6-month follow-up.Patients in the “Me cuido y me siento mejor” primary care clinics would report higher treatment acceptability than patients in the enhanced usual care primary care clinics, at 6-month follow-up.

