### Sample size

The meta-analysis conducted by Huang et al. [39], about the effectiveness of collaborative care in diabetic and depressed patients treated in primary health care showed that 27% of patients in the usual group responded to depression treatment. Considering a two-tailed alpha of 0.05, a statistical power of 80%, 4 clusters per treatment group, 38 participants per cluster, and assuming an intraclass correlation coefficient (ICC) of 0.02 –a more conservative ICC than that reported by Adams et al.– [40] with a design effect of 1.74, we calculated a minimum detectable difference of 23% between the treatment groups, with the expectation that 50% of the members of the active group will respond to depression treatment. Anticipating 15% attrition at follow-up, this study will need to recruit 45 participants in each of the 8 clusters (360 cases in total).

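### The primary random-effects logistic model compares 4 with 4 clinics and names no small-sample method; with the usual Wald z test its type I error is about 9% at the planned ICC of 0.02

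*Protocol article*

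**What the plan says.** The Statistical methods section of the protocol article fixes the analysis of dichotomous outcomes, the main outcome included: "we will fit logistic random effects regression models to reflect the grouped nature of the data and will report OR", with 95% CI and p value. Continuous outcomes follow the same strategy with linear random-effects models. The sections on additional analyses and on missing data add adjusted estimates, repeated-measures mixed models, per-protocol analyses and, if judged pertinent, multiple imputation pooled by Rubin's rules. None of them names a degrees-of-freedom or standard-error correction, a clinic-level analysis or a permutation test.

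The Sample size section sets the design: "Considering a two-tailed alpha of 0.05, a statistical power of 80%, 4 clusters per treatment group, 38 participants per cluster", "assuming an intraclass correlation coefficient (ICC) of 0.02", and a design effect of 1.74, from which "we calculated a minimum detectable difference of 23% between the treatment groups" (27% versus 50%). Under Sequence generation, the four clinics in each of two municipalities are allocated 1:1.

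**The concern.** Treatment is assigned to clinics, so the information on between-clinic variation comes from eight units, with 8 - 2 = 6 degrees of freedom once the two arm means are fitted. A Wald z test treats the standard error as known. With eight clinics it is not: the clinic variance is poorly estimated, and in the simulation below its estimate is zero in about 40% of data sets at ICC 0.02. Each time this happens the analysis reverts to treating patients as independent. The result is a test that rejects too often and an interval that is too narrow, for the trial's one confirmatory comparison. A borderline significant primary result would be hard to defend if the small-sample method were chosen only after the data were seen.

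**Working it through.** **Inputs (Sample size section).** Two-sided alpha 0.05, power 80%, 4 clinics per arm, 38 analysed per clinic (152 per arm), ICC 0.02, response 27% versus 50%.

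**The plan's own figures.**
- Design effect: 1 + (38 - 1) × 0.02 = 1.74, as stated.
- Recruitment: 38 / 0.85 = 44.7, so 45 per clinic and 360 in total, as stated.
- Effective n per arm: 152 / 1.74 = 87.36. SE = sqrt[(0.27 × 0.73 + 0.50 × 0.50) / 87.36] = 0.0715, and 0.23 / 0.0715 = 3.215.
- Normal test: power at 23 points is 89.5%, and the detectable difference at 80% power is 20.0 points (20.3 with a pooled variance).
- Formula that adds one cluster per arm: k = 1 + (1.96 + 0.84)² × 0.4471 × 1.74 / (38 × 0.23²) = 4.04 clusters per arm. With k = 4 the detectable difference is 23.1 points and power at 23 points is 79.5%. Of the variants tried, this comes closest to the stated 23.

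**Type I error of the planned model with a Wald z test.** Data sets were simulated with no effect, 8 clinics of 38 and 27% response. Each was fitted by maximum-likelihood random-intercept logistic regression with Gauss-Hermite quadrature, and the statistic was compared with 1.96. There were 3,000 to 6,000 data sets per scenario, with Monte Carlo error of about 0.4 points.

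| ICC | Wald z type I error |
|---|---|
| 0 | 4.1% |
| 0.005 | 5.8% |
| 0.01 | 7.4% to 7.7% |
| 0.02 | 8.9% to 9.4% |
| 0.03 | 9.9% |
| 0.05 | 11.8% to 12.4% |

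At ICC 0.02:
- 95% CI coverage is 90.1% to 90.9%.
- With 45 per clinic, type I error is 9.8%.
- If half the clinic variance lies between the two municipalities, which the allocation balances, type I error is 6.6%.
- Linear random-effects models with z tests give 9.6% by ML and 7.3% by REML.

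**Alternatives at ICC 0.02.**

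| Method | Type I error | Power, 27% vs 50% | Detectable difference at 80% |
|---|---|---|---|
| Mixed model, t on 6 df | about 3.5% | about 79% to 81% (simulated) | about 23 points |
| Clinic-level t test, 6 df | 4.5% to 4.7% | 76.4% (formula), 75.6% (simulated) | 24.1 points |
| Clinic-level with municipality, 5 df | not simulated | 73.0% (formula) | about 25 points |

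The 5-df row assumes that municipality explains no clinic variance. If it explains half (residual ICC 0.01), the same formula gives about 82% power and 22.3 points.

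**Interval width.** The t(6) critical value is 2.447, and 2.447 / 1.960 = 1.25. For the same SE, intervals are about 25% wider on the log-odds scale.

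**Permutation within municipality.** There are 6 × 6 = 36 arrangements, so the smallest two-sided p value is 2 / 36 = 0.056.

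**The case against.** The strongest reply is that the article names a model class and an effect measure, not a Wald z reference. A degrees-of-freedom method could sit in an analysis plan that is not shown. That is a fair limit, and the 9% must be read as conditional on the usual large-sample test. But the model, the OR, the interval and the p value are already fixed for a comparison of eight clinics, and that model in its usual form does not hold 5% at the protocol's own inputs.

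Second, the size depends on the ICC. The protocol calls 0.02 conservative, and inflation is small at 0.005 and absent at 0. This stands, and it is why a range is given. It would be wrong to say that every interval under-covers.

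Third, a reader might infer that the sample size section pays for a small-cluster correction that the analysis then omits, so that the two sections contradict each other. The documents do not support this. No formula is named, the match to one cluster lost per arm is inference, and a conservative sample size does not conflict with the analysis model.

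Fourth, a reader might infer that the stated 80% power is wrong under any valid test. It is not: the mixed model referred to t on 6 df keeps about 80% at 23 points. The shortfall belongs to the clinic-level t test alone.

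Finally, reporting an OR when the hypothesis concerns proportions is a matter of preference, since percentages by arm are reported too. The Hypotheses wording, "The proportion of patients with improvement in depressive symptoms will be 23% higher in the" intervention clinics, is a slip in expression that the 27% and 50% in the Sample size section settle as percentage points.

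**Conclusion.** The concern holds in conditional form. With eight clinics, 38 patients each and an ICC of 0.02, the planned logistic random-effects model with an uncorrected Wald z test has a type I error of about 9% and 95% CI coverage of about 90%. Over ICC 0 to 0.05 the error runs from about 4% to about 12%. It is about 6.6% at ICC 0.02 if half the clinic variance lies between municipalities. The secondary continuous outcomes are affected similarly. The figures assume equal clinic sizes and the large-sample reference that the article neither states nor replaces. The detectable difference of 23 points is not shown to be wrong.

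**What to change.** In the Statistical methods section, name in advance a method whose inference rests on the number of clinics. There are two options.

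1. Keep the random-effects models, but take tests and intervals from a t distribution with between-clinic degrees of freedom (about 6). Use Kenward-Roger or a similar method for the linear models, and apply the same cap on degrees of freedom when imputations are pooled. The sample size statement can then stay. This option is somewhat conservative at ICC 0.02 (about 3.5%), but about 6% at 0.05 and about 10% at 0.10.
2. Analyse the eight clinic response proportions by arm, with t on 6 df, or 5 df if municipality is included. Type I error stays near 5% over the ICCs simulated with 6 df. The Sample size section should then give about 76% power at 23 points, or a detectable difference of about 24 points (6 df). With 5 df the figures are about 73% or 25 points if municipality explains no clinic variance.

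A permutation test that respects the municipality allocation should not be the primary test, because it cannot reach 5%.

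The cost is a change of wording, wider intervals (about 25% on the log-odds scale for the same SE) and less power than the uncorrected test. No more patients are needed.

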#### Interim analyses

No interim analyses are planned.

#### Methods for additional analyses (e.g. subgroup analyses)

Regarding the evaluation of the effects of the intervention (i.e. analysis of the main and secondary outcomes), raw and adjusted effect estimates will be presented. The adjustment will involve sociodemographic variables with a well-known diagnostic value (i.e. sex and age), complemented with covariables to reflect the potential imbalance between the intervention groups.

Additional analyses will consider the fit of repeated measures mixed effects models to determine whether the effect of the intervention differs over time, taking into account the correlation between the measures of a single participant, as well as the study design. The potential moderating effects of sex and age will be considered in these analyses.

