## Outcomes

### Primary outcome

#### Depression improvement

Defined as a 50% reduction in a participant’s Patient Health Questionnaire-9 Item (PHQ-9) score compared to the baseline [36]. The summary measure for each group will be the percentage of participants who respond to their depression treatment at 6-month follow-up. Even though the primary outcome is taken at 6-month follow-up, this measure will also be reported at 3- and 12-month follow-up.

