#### Social solving problem skills

Defined as a patient’s score on the Positive Problem Orientation and Rational Problem Solving Style subscales of the Social Problem-Solving Inventory – Revised Short Form (SPSI-R:S) [38]. The summary measure for each group will be the mean score of the participants at 3-, 6-, and 12-month follow-up.

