### Recruitment

A trained recruiter will be allocated to each of the primary care clinics taking part in the trial. Recruiters will contact potential participants in-person – at the primary care clinics’ waiting rooms – or remotely (e.g., via telephone call and based on lists of registered cardiovascular patients at the primary care clinics), if in-person contacts are not possible. Recruiters will inform patients of the study, evaluating the initial eligibility criteria and administering the informed consent. After securing the patients’ written informed – or verbal, if in-person contact is not possible –, and if they meet the initial eligibility criteria (e.g. PHQ-9 ≥ 15), potential participants will be contacted again by the recruiters for an in-person (or remote – e.g., telephone call) assessment 1 week later. During this period, recruiters will send reminders to potential participants using the available means of contact. In the reassessment, those with a PHQ-9 ≥ 15 will be recruited for the trial and will be invited to continue by answering the baseline evaluation.

To ensure a sufficient recruitment flow, recruiters will work every day of the week in the morning, when most people attend health care centers. These activities will be supervised by a person in charge of recruitment, who will be in close contact with members of the research team in charge of fieldwork. To facilitate the work of the recruiters, signs, leaflets, and banners with basic information about the study will be on display, inviting potential participants to contact the recruiters. Each recruiter will remain in the allocated primary care clinic until he/she has recruited 45 participants. Additionally, if in-person recruitment is not possible, the lists of registered cardiovascular patients at the primary care clinics will be obtained for the remote contact of potential participants.

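### The adjusted model fixes only sex and age, leaves the other covariates to observed imbalance, and prespecifies no baseline outcome score

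*Protocol article*

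**What the plan says.** The general methods section of the protocol article specifies random effects logistic and linear models without covariates and adds: "We will check the balance between the baseline characteristics of the intervention groups". The section on additional analyses then states that, for main and secondary outcomes, "raw and adjusted effect estimates will be presented". On the content of the adjusted model it says: "The adjustment will involve sociodemographic variables with a well-known diagnostic value (i.e. sex and age"), followed by "complemented with covariables to reflect the potential imbalance between the intervention groups". No candidate list, threshold or test is given, and no baseline outcome score is named.

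The outcomes concerned are of three kinds:

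- **Response (primary).** "Defined as a 50% reduction in a participant’s Patient Health Questionnaire-9 Item (PHQ-9) score compared to the baseline". The time point is six months: "The summary measure for each group will be the percentage of participants who respond to their depression treatment at 6-month follow-up".
- **Recovery.** A PHQ-9 below 10 at follow-up, whatever the starting score.
- **Scores compared as follow-up means.** For problem-solving skills, for example: "The summary measure for each group will be the mean score of the participants at 3-, 6-, and 12-month follow-up". SF-12 is handled in the same way.

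A baseline PHQ-9 exists for every participant, because it is the entry criterion: "those with a PHQ-9 ≥ 15 will be recruited for the trial" after the one-week reassessment.

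**The concern.** The article does not simply leave the covariates to a later analysis plan. It states a way of choosing them, and that way is weak for three reasons.

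First, a covariate enters because the arms happen to differ on it, not because it predicts the outcome. With four clinics per arm, chance differences are common, so the final model would usually be settled only once the data are in.

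Second, the baseline value of the outcome is the natural covariate for a score compared at follow-up, and for a fixed cut-off that patients approach from different distances. It enters here only if it happens to look imbalanced.

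Third, two estimates are promised for each outcome without an explicit statement of which one carries the conclusion. At stake are precision on several secondary outcomes and the standing of the adjusted estimate.

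**Working it through.** **1. The plan's own figure.** Inputs from the sample size section: 27% against 50%, two-sided alpha 0.05, power 80%, 4 clusters per arm, 38 per cluster, ICC 0.02.

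- Design effect = 1 + (38 − 1) × 0.02 = 1.74, as stated.
- With one cluster per arm deducted as a small-sample allowance (my assumption; the article does not give its formula), effective n per arm = 3 × 38 / 1.74 = 65.5.
- Detectable difference = (1.96 + 0.84) × √[(0.27 × 0.73 + 0.50 × 0.50) / 65.5] ≈ 0.231, or 23.1 points. This agrees with the stated 23. Using all four clusters gives 20.0.
- The stated figure does not depend on covariates, so this point changes no number in the plan.

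**2. Gain for the primary outcome.** The article gives no baseline-to-follow-up correlation, so a range is assumed, with baseline PHQ-9 limited to 15–27, follow-up SD 6 and overall response 38.5% (midway between 27% and 50%). The detectable difference is multiplied by about √(1 − R²).

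| Assumed correlation | R² for response | Detectable difference (points) |
|---|---|---|
| 0.2 | 0.000 | 23.1 |
| 0.3 | 0.005 | 23.1 |
| 0.4 | 0.023 | 22.9 |
| 0.5 | 0.058 | 22.5 |
| 0.6 | 0.112 | 21.8 |

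The largest gain is 23.1 − 21.8 = 1.3 points. It is small because a higher baseline raises the expected follow-up score but also raises the score that counts as response, and the two largely cancel.

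**3. Recovery.** Here the cut-off does not move with baseline. A patient entering at 15 must fall at least 15 − 9 = 6 points, and one entering at 27 at least 27 − 9 = 18. As an illustration, take baseline mean 18.3, SD 2.9, follow-up SD 6, correlation 0.4 and 27% response in the control arm (all but the 27% assumed). Control recovery is then about 40% for baselines of 15–17 and about 10% for 21–27. A lower correlation gives a flatter gradient and a higher one a steeper gradient.

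**4. SF-12 and SPSI-R:S means.** Adjusting for the baseline score multiplies individual-level variance by 1 − ρ².

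| Assumed ρ | 1 − ρ² | Variance cut | Equivalent extra patients |
|---|---|---|---|
| 0.3 | 0.91 | 9% | 10% |
| 0.5 | 0.75 | 25% | 33% |
| 0.7 | 0.51 | 49% | 96% |

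Simulated trials with the planned layout (8 clusters of 38, ICC 0.02, cluster-level t test on 6 df) show the same pattern. The SD of the estimated difference fell from 0.156 to 0.149, from 0.163 to 0.142 and from 0.170 to 0.130.

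**5. How data-dependent the selection is.** With k independent baseline variables tested at 5%, the chance that at least one is flagged is 1 − 0.95^k: 23% for 5, 40% for 10 and 64% for 20. In the simulation, with 11 candidates and clustering ignored in the balance tests, about 80% of trials flagged at least one.

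Type I error in the same simulation, with no true effect:

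| Analysis | Type I error |
|---|---|
| Fixed baseline-adjusted model | 5.1–5.4% |
| Mechanical 5% imbalance rule | 3.6–4.1% |
| Smallest p value among the raw and adjusted analyses | 9–11% |

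The mechanical rule also lowered the SD of the estimate (to 0.146, 0.147 and 0.143). What it loses is a calibrated test and a model known in advance.

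**The case against.** The strongest reply has several parts.

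- **Baseline PHQ-9 matters little for the primary outcome.** This stands. A reader might infer that the trial gives up its strongest predictor of response, but response is already relative to baseline and the range is cut at 15. Chance imbalance matters little too. With an assumed SD of 2.86 and 45 per clinic (design effect 1 + 44 × 0.02 = 1.88), the SE of the arm difference in baseline PHQ-9 is 2.86 × √(2 × 1.88 / 180) = 0.41 points. At correlation 0.4, a one-SE imbalance moves response by roughly 0.6 to 0.75 percentage points, against a planned 23. Nor is chance imbalance a bias over repeated randomisations.
- **Baseline scores are not barred.** This stands. They may enter through the imbalance route, so they are not prespecified rather than excluded.
- **False positives are not inflated by the stated procedure.** This stands for a mechanical rule. The 9–11% arises only if analysts choose freely among estimates, which the article does not propose. The raw estimate is always reported, so adjustment cannot hide it.
- **The layout implies that the raw estimate leads,** since adjustment appears under additional analyses. This is a fair reading, but it is left to inference.
- **Covariate lists belong in an analysis plan.** This stands for detail. Here a rule is stated, so a later plan would have to replace it rather than fill it in.
- **Not every continuous secondary outcome can gain.** This stands. Acceptability rates the treatment received and has no baseline value. Baseline SF-12 and SPSI-R:S are inferred from the mention of a baseline evaluation whose contents are not listed.

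**Conclusion.** The point holds in limited form. The stated adjustment rule is open-ended and driven by imbalance, no baseline outcome score is prespecified, and the primary estimate is not named outright. For the primary outcome the practical loss is small: 0% to 11% of response variance and at most about 1.3 points of detectable difference, under assumed correlations of 0.2 to 0.6. The loss is larger for recovery and for the SF-12 and SPSI-R:S means (9% to 49% of individual-level variance at assumed correlations of 0.3 to 0.7).

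A reader might also compare the responder analysis with a baseline-adjusted mean PHQ-9, where it keeps only about 58% to 63% of the information under assumed correlations of 0.3 to 0.5. That is the price of dichotomising, not of the adjustment set, and adding a mean PHQ-9 outcome is a matter of preference. The documents do not show that the primary result would be biased or its error rate inflated.

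**What to change.** In the section on additional analyses, replace the imbalance clause with a fixed set for each outcome:

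- all outcomes: sex, age and municipality, the unit within which clinics are allocated 1:1;
- response and recovery: add baseline PHQ-9 as a continuous variable;
- SF-12 and SPSI-R:S: add the baseline value of the same measure;
- blood pressure and glycosylated haemoglobin: add the baseline value where a record exists. The article takes these data retrospectively from clinical records and does not say that every patient has a baseline value.

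State before unblinding which estimate, raw or adjusted, is primary for each outcome. The baseline balance table can stay as description.

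The change needs wording only, and baseline PHQ-9 is already collected. There are two costs. With eight clusters the list must stay short. And the adjusted odds ratio is conditional on the covariates, so a standardised risk difference should be reported beside it.
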